### Blinding

It is intended that both patients and outcome assessors are blinded to treatment group. Group allocation concealment will be maintained by using a centralised web-based randomisation service. Outcome assessments will be performed by local research support staff who will be blinded to treatment allocation. After each assessment, the researcher will be asked to record whether they have unintentionally become aware of treatment allocation. Success of outcome assessment blinding will be reported. Therapists delivering the intervention will be instructed not to inform patients if they are in the ‘intervention’ or the ‘control’ group. Participants will all be given a general patient information sheet prior to randomisation which does not describe differences in CueS wristband function between the intervention and control groups. After randomisation participants will receive a group-specific patient information sheet with more details about what to expect from their CueS wristband. This is to reduce control group expectations that prompts could occur.

### Study withdrawal

No specific study withdrawal criteria have been set. Participants may stop the therapy programme or withdraw altogether from the study at any time without giving a reason. Should a patient decide to stop the therapy programme, the data already collected will be used in the analysis unless consent is specifically withdrawn and their permission will be sought to continue with the outcome assessments.

### Recording and reporting of adverse events

All adverse events will be recorded for the duration of each participant’s involvement in the study but only serious adverse events (SAEs) will be specifically reported. Recording will take place at the outcome assessments by inclusion of the following question: “Are there any new medical problems since the last study assessment?” We will specifically enquire about the presence of pain in the affected upper limb and overall fatigue. Events considered to be SAEs will subsequently be documented onto a separate study SAE form, including a report of causality and expectedness.

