### Exclusion criteria

Severely reduced upper limb function which results in inability to lift the affected hand off the lap when sitting.Unable to follow the programme due to significant cognitive impairment or communication difficulties.Other significant upper limb impairment e.g. fixed contracture, frozen shoulder, severe arthritis, upper limb pain that inhibits participation in the programme.Diagnosis likely to interfere with rehabilitation e.g. registered blind, severe visual problems as a result of stroke, palliative treatment approach being provided.Unable to sense both CueS wristband vibratory prompts and visual display.

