Before randomisation, the patients’ clinical NHS occupational/physiotherapist will confirm that the patient will be able to feel the CueS vibratory prompt and/or see the LED display. For the first 3 days of the 4-week programme, the CueS wristband will only monitor affected upper limb movement and no prompts will be delivered. At the patient’s first review for the study their NHS therapist will use the data collected from the previous 3 days to agree initial baseline prompt settings with the patient and discuss how frequently prompts should be delivered. The maximum frequency for receiving a prompt (i.e. minimum time allowed between prompts) will be set at a default of 60 minutes but can be adjusted from 30 minutes to 4 hours. The default prompt threshold will be the mean activity value or “signal vector magnitude” from across the first 3 days plus 5 %, i.e. a prompt will be delivered if the sum of arm movement activity falls below this target threshold throughout the minimum pre-set interval allowed between prompts. The NHS therapist will review the therapy programme and CueS data report twice weekly. If prompts were triggered since the last visit, they will discuss continuing with the same or a lower threshold and review possible arm activity responses. If no prompts were triggered they will discuss selection of a more challenging monitoring level by increasing the threshold to the mean plus 10 % or mean plus 20 %. If too many prompts were received they will lengthen the prompt frequency interval according to the number of prompts per day which is acceptable to each patient. The aim is to encourage arm activity which is in the upper half of the patient’s individual range of ability without triggering inconvenient prompts or precipitate desensitization to prompts. At each review session the therapist will complete a therapy review form to capture safety reporting, times when the CueS wristband was not worn, prompt information and any adjustment to prompt threshold settings.

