### Outcome assessments

Outcomes will be assessed at 4 weeks (+/− 3 days) and 8 weeks (+/− 5 days) following day 1 of the therapy programme. Assessments will be undertaken by research support staff who have not been informed of participant group allocation.

The following data will also be collected: stroke dependency (measured by the Modified Rankin Scale [14], Barthel Activities of Daily Living Index [15]); pain and fatigue (measured by a numerical visual analogue scale, 0–10); upper limb function (measured by the Action Research Arm Test [17]); real world upper limb activity (measured by the Motor Activity Log [18]); arm strength (measured by the Motricity Index [19]); and unilateral spatial neglect (measured by the Star Cancellation Test [20]).

Participants will be provided with a standard wrist-worn accelerometer during the week 4 and week 8 assessments, which is to gather upper limb activity outcome data for the next 3 days. They will then send it back to research support staff in the envelope provided.

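### The general adverse event question at the 4- and 8-week visits asks only about new problems, which is narrower than the promise to record all adverse events, so worsening of existing conditions may be under-ascertained, most clearly in weeks 4 to 8

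*Protocol article*

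**What the plan says.** Under Recording and reporting of adverse events, the protocol article sets the scope: "All adverse events will be recorded for the duration of each participant’s involvement in the study". Only serious events are then singled out for reporting. The same section gives the method: "Recording will take place at the outcome assessments by inclusion of the following question", and the question printed is "Are there any new medical problems since the last study assessment". It adds: "We will specifically enquire about the presence of pain in the affected upper limb and overall fatigue". Events judged serious go on to a separate form that covers causality and expectedness.

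Three other sections bear on the point:

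- Outcome assessments lists "pain and fatigue (measured by a numerical visual analogue scale, 0–10") among the measures at 4 and 8 weeks. Baseline assessment lists the same two scales.
- CueS wristband says: "At each review session the therapist will complete a therapy review form to capture safety reporting". Reviews are twice weekly, and Upper limb therapy programme sets the programme at 28 days.
- Study objectives makes the reporting of serious adverse events in each group one of the aims.

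**The concern.** The stated scope is all adverse events, but the scripted question covers only new ones. A participant whose long-standing heart, lung or seizure disorder flares up, or who is admitted for it, can truthfully answer no. So can a participant whose mild arm stiffness from before the stroke has become worse. Such participants can be enrolled: the relevant exclusion reads "Other significant upper limb impairment e.g. fixed contracture, frozen shoulder, severe arthritis, upper limb pain that inhibits participation in the programme", which leaves milder arm problems eligible, and general comorbidity is not excluded unless it is likely to interfere with rehabilitation.

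At stake is the count of serious adverse events by group, which is a feasibility objective and will be read when the later trial is planned. An event that is never elicited may never be assessed for seriousness.

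**Working it through.** The document gives no adverse event rate, so there is no figure to reproduce. The check sets the described recording routes against the kinds of event they would pick up.

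**Timing.** Outcome visits are counted from day 1 of the programme.

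- Therapist reviews: 28 days at one every 3–4 days, so 28 / 3.5 = about 8 contacts.
- Follow-up after the programme: 8 × 7 − 28 = 28 days, which is 28 / 56 = 50% of the planned follow-up. With the ±5-day window on the 8-week visit, this runs from 23 to 33 days.

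**Coverage by kind of event.**

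| Kind of event | Weeks 0–4 | Weeks 4–8 |
|---|---|---|
| New medical problem | Scripted question at week 4; therapist form | Scripted question at week 8 |
| Arm pain or fatigue, new or worse | Separate enquiry; 0–10 score against baseline; therapist form | Separate enquiry; 0–10 score against earlier scores |
| Other worsening of an existing condition, including admission for known disease | Therapist form (wording not shown); otherwise if volunteered | If volunteered |

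The first two rows are covered throughout. The pain and fatigue enquiry asks about presence, not new onset, and the serial scores make worsening measurable. In the third row, weeks 0–4 have a possible second route whose content cannot be judged. In weeks 4–8 no described route asks about such events.

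**Other safeguards.** The monthly safety review in Data monitoring works on data already collected. That section also expects local clinicians to watch over participants, but does not describe this as a route by which events reach the study record. Serial arm function and strength scores would show a decline in the arm, but as an outcome measure and not as a recorded event.

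**Consistency between sections.** The adverse event section places recording at the outcome assessments and does not mention the therapist form. The form appears under CueS wristband, beside prompt settings. Sham CueS wristband gives controls the same twice-weekly visits to review practice activities but does not mention the form. The article therefore does not state whether safety reports are taken by the same routes in both groups.

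**Scale of one event.** 60 participants randomised 1:1 gives 60 / 2 = 30 per group, and 1 / 30 = 3.3 percentage points. This is the effect of a single missed serious event on one group's proportion. It does not estimate how many are missed.

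**The case against.** The strongest reply is that the article condenses a fuller protocol. Definitions of adverse events, the form's text and staff guidance may sit there and may already count worsening. The question is an open lay prompt, and many people admitted to hospital would mention it. It is identical in both groups, assessors are meant to be blinded, and no comparative statistics are planned. Much of this stands. The absence of definitions is not a fault here, and no bias between groups is shown. But the article prints the question itself, and its wording is narrower than the scope stated in the preceding sentence.

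A reader might infer more than the document supports:

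- *That this is the only safety enquiry, so worsening is simply not elicited.* The therapist form is a second route during the programme, and pain and fatigue are asked about directly.
- *That the events missed are those most likely to be caused by more arm use.* Aggravation of a mild arm problem would mainly show as arm pain, which is asked about and scored.
- *That serious event forms arise only from answers to this question.* The section does not limit the source.
- *That a number of missed serious events can be given.* Any such number needs an assumed event rate, an assumed share that are exacerbations and an assumption that every one goes unreported. The document supplies none of these.
- *That controls have no therapist safety form.* The article is silent on this, which calls for clarification and does not establish a difference.

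**Conclusion.** The mismatch is real but limited. The plan promises to record all adverse events and fixes a general question that, taken literally, asks only about new ones. The consequence is possible under-ascertainment of worsening other than arm pain and fatigue. It is clearest in weeks 4 to 8, about half the planned follow-up, when no other general route is described. Serious event counts could be too low as a result. By how much cannot be derived from the document, and the lower end of any range is near zero if participants or clinicians report such events unprompted. The conclusion assumes that the printed question is used as worded and that no wider prompt on the unseen forms supplements it at the outcome visits.

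**What to change.** Reword the scripted question at both outcome visits so that it asks about any new medical problem, any worsening of an existing one, and any hospital attendance or admission since the last study assessment. Record all of these as adverse events. Reconcile the adverse event section with the CueS wristband section: say whether the therapist review form is a recording route for adverse events, and state that the same routes apply in the intervention and control groups.

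The cost is one sentence on the assessment form, a short clarification of the protocol and notification of the amendment. A few more background events will be listed. Three participants had been enrolled at publication, so the date of the change should be noted to show which assessments used which wording.

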### Data management

Data will be recorded locally on study-specific documents and transferred to the coordinating centre via an industry-standard secure online database, using a pseudo-anonymised study identification code to link individual participants with their local health records. All paper copies of study documents will be retained at local sites and stored securely for 5 years in line with sponsor policy. The online database is encrypted and only accessible via individual passwords and meets current industry Good Clinical Practice standards. It has been certified by the Lloyd’s Register Quality Assurance according to the international information security norm ISO 27001:2013 and provides its services in accordance with the NEN7510 norm for information security in healthcare (https://castoredc.com/security-statement/).

### Data monitoring

Interim safety and efficacy data will not be formally reviewed against pre-determined criteria for stopping early as this study is a feasibility pilot. A formal data monitoring committee or equivalent body will not be convened, but safety data will be prospectively reviewed at monthly project management meetings with the chief investigator. The well-being of individual participants will be closely monitored by clinicians as they will still be patients within a local clinical service.

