### Inclusion criteria

Age ≥ 18 years.Over 48 hours but less than 3 months post stroke onset.New reduced upper limb function on one side.Able to provide informed consent to participate in the study.Living within the community services catchment area of a participating study centre.Receiving at least twice weekly NHS therapy review which is planned to continue for 4 weeks from the start of the intervention period.

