#### Upper limb therapy programme

The upper limb therapy programme will be delivered by the patients’ NHS physiotherapist or occupational therapist. The programme will last for 28 days in total, which has been selected as a pragmatic interval to achieve >20 hours of upper limb activity practice in line with findings of a recent Cochrane review [24]. The programme has been designed to support and work with normal NHS upper limb therapy programmes. The aim is to increase the use of the affected upper limb and integrate upper limb activities undertaken in therapy into normal daily routines.

At the initial therapy session, each participant will be provided with a participant handbook which will contain their individualised upper limb therapy programme as it progresses over the 4-week period. The therapists will support the participant to identify a range of goal-directed upper limb activities which reflect part or whole movements needed to undertake a specific activity e.g. reaching to pick up a glass. These activities will be recorded by participants or their relatives on a daily activities log in their participant handbook. The daily activities log will remind participants of activities to practise. The continuing relevance of activities will be reviewed and progressed over the 4 weeks at twice weekly face-to-face occupational therapy or physiotherapy review sessions (i.e. every 3–4 days). It will be left up to the participants to decide how often and when they wish to practice, but all will be informed that additional practice up to an hour every day may improve recovery.

Any usual clinical treatment will continue. In addition, participants will be requested to record whether they have received any upper limb therapy during usual care therapy on their daily activities log sheet. Usual care upper limb therapy is face-to-face therapy provided by an occupational therapist, physiotherapist or therapy assistant.

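### After week 4 the article states no way of finding serious adverse events in participants who miss the week 8 assessment

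*Protocol article*

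**What the plan says.** All references are to the protocol article.

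- **What is promised.** Under Recording and reporting of adverse events: "All adverse events will be recorded for the duration of each participant’s involvement in the study". The Study objectives include reporting SAEs in each group over the course of the study.
- **How events are found.** The same section places recording at the outcome assessments, through one open question about new medical problems since the previous assessment. The timing is under Outcome assessments: "Outcomes will be assessed at 4 weeks (+/− 3 days) and 8 weeks (+/− 5 days) following day 1 of the therapy programme".
- **A second route.** The CueS wristband section has the therapist complete a form at each twice-weekly review, and safety is one of the items it captures. These reviews belong to the therapy programme: "The programme will last for 28 days in total". Eligibility likewise covers this period only: "Receiving at least twice weekly NHS therapy review which is planned to continue for 4 weeks from the start of the intervention period".
- **Oversight.** Data monitoring states that "A formal data monitoring committee or equivalent body will not be convened", but also that "safety data will be prospectively reviewed at monthly project management meetings with the chief investigator". It then adds: "The well-being of individual participants will be closely monitored by clinicians as they will still be patients within a local clinical service".
- **Stopping.** Under Study withdrawal, "Participants may stop the therapy programme or withdraw altogether from the study at any time without giving a reason". Those who stop the programme are asked for permission to continue with assessments.

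**The concern.** The promise covers the whole of each person's participation, but the stated method depends on attendance. Up to week 4 there are two routes. From then on there is one, the participant's own answer at the week 8 visit. A participant who has died, been readmitted, had another stroke or declined the visit may not be there to give it, and these are the people in whom serious events are most likely.

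SAEs by group and attrition by group are both objectives. If one arm loses more participants because of harm, the stated method could record fewer of that arm's SAEs. The safety summary carried forward to the definitive trial would then look better than it should. Monthly review cannot correct this, because it works from recorded events, and the Auditing section rules out regular site visits for monitoring.

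**Working it through.** **Inputs from the article.** Programme of 28 days; assessments at week 4 (±3 days) and week 8 (±5 days) from day 1 of the programme; 60 participants allocated 1:1, so 30 per arm; four sites; 15 months; one participant per site per month. **Not given:** the proportion who will miss week 8, and the SAE risk in those people. Both are assumed below, over a range.

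**1. The plan's own figure.** 4 sites × 15 months × 1 = 60, which matches the recruitment target. The point below uses 60 only for scale.

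**2. Routes by period.**

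| Period | Therapist form | Assessment question | Stated route if the assessment is missed |
|---|---|---|---|
| Day 1 to week 4 | Yes, twice weekly | Week 4 | Therapist form |
| Week 4 to week 8 | None; programme has ended | Week 8 | None |
| 3 days of accelerometer wear after week 8 | None | None | Not applicable; no question follows |

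The second period is 56 − 28 = 28 of 56 days, or 50% of follow-up.

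**3. Interval between the two questions.** Week 4 falls on days 25 to 31 and week 8 on days 51 to 61.
- Shortest: 51 − 31 = 20 days
- Nominal: 56 − 28 = 28 days
- Longest: 61 − 25 = 36 days

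For someone who attends both visits, an event soon after the first is recorded up to about 36 days later, but it is asked for.

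**4. Participants with no stated route after week 4.** Number = 60 × assumed non-attendance.

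| Assumed non-attendance | No stated route | Asked at week 8 |
|---|---|---|
| 5% | 3 | 57 |
| 10% | 6 | 54 |
| 20% | 12 | 48 |
| 30% | 18 | 42 |

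**5. What that could hide.** One unrecorded SAE in an arm of 30 is 1/30 = 3.3 percentage points. If each of m non-attenders independently has probability p of an SAE after week 4, the chance that at least one SAE has no stated route is 1 − (1 − p)^m. With m = 6 and p = 10% this is 1 − 0.9^6 = 0.469. Over m = 3 to 18 and p = 5% to 20% it runs from 0.143 to 0.982. The range is wide because neither input is in the article.

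**6. Where the two recording sections do not meet.** The adverse event section does not mention the therapist form. The form is described within the section on the intervention wristband. The sham wristband section says control visits review practice activities in the same manner, but does not say that the safety form is completed. Whether both arms have the second route in weeks 0 to 4 is therefore not explicit.

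**The case against.** The best reply is that this is an article condensed from a full protocol that is not shown, and that the handling of a death or admission in a non-attender is operational detail. The article also commits to recording all events and to a separate SAE form with causality and expectedness. This carries weight: the full protocol may contain such a procedure. But the article does more than stay silent. It names a method, and that method cannot deliver the coverage promised in the same section.

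Four stronger readings are tempting, and the text does not support them.

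- *Local clinicians replace a monitoring committee.* A reader might infer this from the clinician sentence alone. The sentence before it provides monthly safety review, and the clinician sentence is an addition to that.
- *SAEs after week 4 are missed.* The week 8 question looks back to the previous assessment, so attenders are asked about weeks 4 to 8. For them the cost is delay and recall.
- *Anyone who stops after a problem is lost.* Permission is sought to continue assessments after stopping the programme, and the therapist form is a further route during the programme.
- *Eligibility contradicts the clinician sentence.* That sentence speaks of clinicians and a local service. It does not claim therapist review to week 8, and the entry criterion does not end care at day 28.

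It is also fair to say that no comparative statistics are planned and that attrition by group will be reported, so differential loss would be visible. A reader would still not know how many SAEs occurred among those lost.

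**Conclusion.** The point holds in limited form. After week 4 the article gives one way of finding an SAE, and it works only in those who attend week 8. SAEs in participants who die, are readmitted or otherwise miss that visit may go unrecorded, and monthly review would not see them.

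The number affected is unknown. At an assumed 5–30% non-attendance it is 3–18 of 60 participants. A downward bias in SAE counts by group is possible, not shown: it requires attrition to be related to harm, and a difference between arms requires that relation or the amount of loss to differ. The conclusion also assumes that the full protocol adds no other route. The gap is worth closing because safety by group is a stated objective and the remedy is cheap.

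**What to change.** - **Record check.** For every randomised participant, where consent allows, check the local health record for deaths, admissions and recurrent stroke, and raise SAE forms from what is found. Cover the time from randomisation to the end of the last 3-day accelerometer wear. Starting at randomisation includes anyone who never begins the programme, whose assessments would otherwise have no day 1 to count from. The Data management section already describes a study code that links participants to their local records.
- **Blinding.** Research support staff are the blinded outcome assessors. The check should be done by an unblinded member of the clinical team already in post, or by research support staff only after the participant's final blinded assessment.
- **Reconcile the recording sections.** State in the adverse event section that the therapist form is also a source, and whether it is completed in both arms.
- **Data monitoring.** Word the clinician sentence so that reliance on local care does not stand in for SAE capture after week 4.

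Cost: a few minutes of record review per participant, a short change to the protocol text, and possibly consent wording to cover the check.
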